## Abstract

**Background:**

Traumatic brain injury is a major cause of mortality and morbidity worldwide. It can be worsened by secondary injury particularly with hypoxia or hypotension. Current prehospital guidelines emphasise regular measurement of peripheral oxygen saturation and blood pressure but there is no monitor in use to provide direct information relating to blood flow or oxygen delivery to the brain tissue. This prospective cohort study will assess the utility of near-infrared spectroscopy monitoring in prehospital medicine in demonstrating injury, pathophysiology and associations with long-term functional outcomes.

**Methods/design:**

A prospective cohort study will be conducted in prehospital services where physician/paramedic teams respond rapidly to patients suffering significant traumatic injuries. A study observer accompanying the clinical team will apply non-invasive near-infrared spectroscopy tissue oximetry using a Nonin EQUANOX 7610 Regional Oximetry monitor (TM Nonin Medical, Inc.). This will be applied to patients with traumatic injuries less than 30 minutes old requiring transport. Measurements will be taken at two sites on the forehead and one on the forearm. Clinical teams will be blinded to all monitoring values. Near-infrared spectroscopy tissue oximetry parameters of oxyhaemoglobin%, deoxyhaemoglobin%, total tissue haemoglobin index and regional oxygen saturation will be recorded. Separate statistical analysis relating to time spent with cerebral regional oxygen saturation values < 45% and time series analysis will be performed to demonstrate associations with acute phase outcomes including injuries seen on cerebral imaging, and long-term functional outcomes measured by Glasgow Outcome Score and Extended Glasgow Outcome Score will then be undertaken.

**Discussion:**

This prospective cohort study will demonstrate associations evident from the earliest stages of prehospital treatment between near-infrared spectroscopy tissue oximetry values and both acute and long-term outcomes of patients suffering traumatic injuries. This may provide the basis for future interventional studies utilising near-infrared spectroscopy tissue oximetry to guide prehospital trauma care.

**Trial registration:**

This trial is registered with the Australian and New Zealand Clinical Trials Registry. The registration number is ACTRN12611001124921.

## Background

Traumatic brain injury (TBI) is a significant cause of death and severe disability [1]. Estimates suggest that long term costs of caring for people with moderate and severe TBI add $8.6 billion to health spending per year in Australia [2]. Despite advances in hospital care of patients with TBI, minimal improvements in outcome have been evident over the last twenty years [1].

In the setting of TBI, it is not only the initial injury that is responsible for patient outcome. After the initial insult, the brain is susceptible to further damage if normal physiologic conditions are not restored. Such insults include low blood pressure or hypoxia [3,4]. The primacy of hypoxia and hypotension in the debate has guided the development of consensus guidelines for prehospital management of patients with TBI with an emphasis on regular blood pressure measurements and checking oxygen saturations [5]. However, having this knowledge to guide monitoring care has not resulted in significant changes to patient outcomes.

Peripheral measurements such as non-invasive blood pressure and pulse oximetry remain relatively crude measurements distant to the tissue of most interest; the brain itself. Additional monitoring options that have become available in the hospital such as jugular venous bulb oximetry, direct tissue oximetry and intracranial pressure measurement are not appropriate to the prehospital environment [6-8]. In the New South Wales metropolitan setting, the time spent in the prehospital treatment phase before reaching a trauma centre averages over one hour [9]. This represents a significant period of vulnerable time where monitoring information relevant directly to cerebral tissue is absent.

Near-infrared spectroscopy (NIRS) tissue oximetry was first described in 1977 and is now used within hospitals [10]. It uses light in the near-infrared spectrum (700–1300 nm) and relies on the interaction of these wavelengths with tissue chromophores to derive information about oxygenated blood in the monitored region. Commercial devices use reflectance spectroscopy. The light is shone into tissues from an emitting light source within a self-adherent probe at the skin. Light entering the tissues interacts with chromophores, with the degree of absorption and scattering specific to the near-infrared wavelength employed. The fraction of transmitted light that returns to the surface is detected within the same probe, with a standard separation between the initial light source and the detector.

Utilising known characteristics of the interaction of particular near-infrared wavelengths with biological tissues allows the calculation of a number of parameters:Oxyhaemoglobin%, (HbO_2_) a measure of haemoglobin carrying oxygen through the tissues;Deoxyhaemoglobin% (HbD), a measure of haemoglobin present but not carrying oxygen;Total tissue haemoglobin index (HbT) – an index (expressed in g/dL) corresponding with blood volume and flow within the sampled tissue; and,Regional oxygen saturation (StO_2_%), providing a measure of the balance of oxygen delivery and utilisation in the tissue under the probe as it adjusts for the influence of chromophores other than oxy- and deoxyhaemoglobin as well as the adjustment for the proportional amounts of arterial and venous blood in the sampled area.

Recent monitors display improved accuracy and time resolution and are therefore spreading into a variety of clinical areas including detection of silent ischaemia in subarachnoid haemorrhage, coronary artery bypass grafting, aortic arch surgery, paediatric cardiac surgery and carotid endarterectomy [11-15].

NIRS oximetry has been utilised in head injury patients although application of the monitor has generally occurred hours after the initial injury. Early work with NIRS tissue oximetry has suggested that it may provide useful information in detecting intracranial haematomas and correlation with direct tissue oximetry. To date this work has been entirely hospital-based [16-19].

A further relatively recent development in the use of NIRS oximetry is the ability to use novel analysis techniques to assess dynamic factors such as cerebrovascular autoregulation. Various approaches such as coherence analysis of spectral waveforms and floating correlation analysis of moving value windows have been described in the assessment of vascular reactivity in subarachnoid haemorrhage, traumatic brain injury, paediatric cardiac surgery and extracorporeal membrane oxygenation [20-24]. Examples of this analysis rely on examination of the trends and patterns seen in the haemoglobin index (HbT) rather than analysis of absolute values of either HbT or rSO_2_.

This study builds on earlier work demonstrating the possibility of obtaining NIRS oximetry monitoring values in the prehospital and transport environments [25]. It will assess the utility of prehospital NIRS oximetry in the monitoring of patients with TBI.

### Study plan

The *hypothesis* is that NIRS tissue oximetry can provide direct real-time cerebral physiological data that provides an insight into rapidly developing brain pathology in TBI and its management, as well as early associations with long-term outcomes. Three aims will be delivered to achieve this:To establish methods of analysing the NIRS tissue oximetry monitoring parameter time series that correspond with evolving pathology in the TBI.To establish the association between NIRS tissue oximetry monitoring parameters and acute pathology in patients with TBI.To establish the association between NIRS tissue oximetry monitoring parameters and the long-term recovery of patients after TBI, as assessed at follow-up to 12 months.

This research will therefore be conducted in a prehospital setting, providing early monitoring data in patients likely to have TBI with a plan for subsequent follow-up data collection to examine both acute and long-term outcomes. Novel analysis methods as featured in Aim 1 will provide better options for demonstrating the associations described in aims 2 and 3.

### Study design and setting

This is a prospective cohort study.

This research will be conducted in a prehospital emergency medical service employing a physician-paramedic model of care to deliver rapid response trauma care and employing both rotary-wing and road transport modalities. The clinical team is capable of providing advanced life support, anaesthesia, intubation and ventilation, blood transfusion and peripheral haemorrhage control manoeuvres along with other critical care interventions at the scene of the accident or during patient transport.

### Inclusion and exclusion criteria

All patients where patient contact is within 30 minutes of the injury and who are being transported to the trauma centre by the prehospital clinical team will be considered for inclusion. Exclusion criteria include:Patients < 1 year old and > 70 years old.Patients with pre-existing neurological disease or neurological trauma.Patients with no mechanism for trauma, (e.g. drowning, medical complaints);Patients with forehead haematomas or lacerations precluding NIRS probe application;Patients where follow-up consent is not later obtained from the patient or family.

Exclusion criteria may be apparent at the accident scene or may be applied upon the collection of additional information that reveals the patient meets exclusion criteria.

### Monitor application

For the purposes of this research, NIRS cerebral oximetry will be applied by a trained researcher as soon as possible after arrival at the patient to ensure the clinical team are able to undertake their standard approach to care. The monitor employed will be a Nonin EQUANOX 7610 Regional Oximetry monitor (TM Nonin Medical, Inc.). This trained observer will apply monitoring probes bifrontally to the forehead of patients and to a peripheral reference site on the forearm (Figure 1). Monitoring will be commenced within a time frame of 30 minutes after the initial injury. The monitoring screen will only show that data capture is proceeding with warning signals if there are issues with sensor contact or signal quality. The EQUANOX 7610 monitor will continuously store the NIRS monitoring data. NIRS monitoring will cease on patient handover at the receiving hospital.

**Figure 1 Fig1:**
[figure not shown]
**Cerebral oximetry probes applied to a volunteer during helicopter transport as part of feasibility testing.**

### Data collection

Data collected by the research nurse, who will be blinded to NIRS monitoring information, will include patient demographics already recorded as a routine (available at the time of the injury) and via hospital follow-up. Trauma incident data including incident time and total prehospital duration will also be recorded in initial case documentation.

### NIRS monitoring data

Each NIRS oximetry probe will continually produce 4 streams of data: StO_2_; HbT; HbO_2_; and HbD with values recorded every 4 seconds. Standard clinical monitoring will be recorded at the same time as the NIRS oximetry data captured by the EQUANOX device. This will include peripheral pulse oximetry, end-tidal capnography (where indicated for patient care), heart rate and non-invasive blood pressure and will be updated on the record every ten seconds. This general observations data will be time-matched to the NIRS oximetry monitoring data to allow direct comparisons of values in data analysis, particularly in the signals analysis related to Aim 1. Clinically relevant information such as any degree of prehospital hypoxia or hypotension will therefore be time-matched to the NIRS oximetry monitoring data.

### Patient event and intervention marking

The data capture system for the NIRS oximetry monitor will also facilitate real-time marking of clinical events and interventions by the study observer. This will include real-time marking of bag-mask ventilation, cardiopulmonary resuscitation, anaesthesia with thiopentone, anaesthesia with ketamine, intubation, institution of mechanical ventilation, administration of vasopressor, transfusion, administration of hypertonic saline and seizure activity. Study observers will also have the ability to mark other potential events deemed clinically relevant. This will provide accurate information on interventions undertaken in a manner that is time-matched to the NIRS oximetry monitoring data. Event marking will be combined with NIRS oximetry monitoring data and general observations monitoring to allow reporting of standard interventions and care as previously described [26]. Patient general observations monitoring information and management and intervention details will be presented in conjunction with all outcome data.

### Early phase outcome data

Patient outcome and follow-up data related to initial findings and hospital stay will be obtained from the hospital by the trial research nurse at a time beyond 30 days from the injury and include: (1) Injury Severity Score (ISS) and Abbreviated Injury Scores (AIS) for each body region [27,28]; (2) injuries identified on independent review of first cerebral imaging by computerised tomography (CT) or magnetic resonance imaging (MRI); (3) 24 hour and 30 day mortality; (4) survival to hospital discharge; and, (5) length of intensive care unit (ICU) stay including number of ventilator days.

### Long-term outcomes

Follow-up by the research nurse will be undertaken via phone interview with the patient or appropriately identified relative as previously described [29] to assess and record (1) Glasgow Outcome Scale score (GOS) and Extended Glasgow Outcome Scale (EGOS) score at 6 and 12 months post injury [30]; (2) Disability Rating Scale (DRS) at 6 and 12 months post injury [31] and, (3) Care and Needs Scale (CANS) at 6 and 12 months post injury [32].

### Power analysis

Pre-existing datasets showing the relationship between prehospital NIRS oximetry values and patient injury outcomes in the context of TBI are lacking. To answer Aim 1, a sample size of 242 subjects with severe TBI will provide 90% power to detect correlation of 0.22 or higher [33] in a 2-sided 0.05 level test of the null hypothesis of no correlation between NIRS cerebral oximetry values and admission Glasgow Coma Score (GCS) adjusting for 29 (approximately 12%) unsuccessful NIRS monitoring data collection attempts (25) in a time series based regression analysis. CareFlight’s historical mission database indicates 1210 total recruits will be required to incorporate 242 subjects with severe TBI.

To address Aims 2 and 3, the same number of subjects will be enough to show an incidence of EGOS 4 at six months post-injury of 56% (95%CI 49% to 63%) and demonstrate a clinically important change in EGOS of 1 point associated with NIRS cerebral oximetry value at 80% power to detect a Cochrane-Armitage test for trend in EGOS groups (30% deceased, 20% poor neurological outcome and 50% good neurological outcome) at significance level of 0.05. The expected proportion of EGOS groups have been taken from the subject characteristics from the Head Injury Retrieval Trial [data under analysis] [29].

As for validation of the model for Aims 2 and 3, we will internally validate the models using bootstrapping methods on 1000 samples.

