### Subgroups for analysis and reporting

Some patients, particularly those with more severe injuries and those of a different age, are more likely to have monitor findings indicating strong associations with outcomes and are therefore of particular interest. Subgroup analysis will be undertaken on patients with severe TBI (first GCS ≤ 12 and Abbreviated Injury Score (Head) ≥ 3), severe traumatic injury (ISS > 15), and paediatric patients (age < 16 years).

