### Data analysis

#### Novel analysis methodology to address aim 1: establishing new analysis methods

A variety of approaches to signals analysis as commonly utilised in biomedical engineering fields will be undertaken. These will include (but not be limited to) time series analysis and pattern recognition and classification undertaken on all monitoring value streams (StO_2_, HbT, HbO_2_ and HbD) for each of the cerebral probes separately, and the peripheral reference probe. These may be matched to ancillary signals including peripheral oxygen saturation and electrocardiograph parameters (RR and QT intervals, RR variability). Comparison may also be made between NIRS oximetry probes. Control group patients with traumatic injuries but no brain injury will be the reference group for analysis of “standard” signals analysis patterns comparisons.

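### The 90% power for Aim 1 belongs to a correlation with admission GCS that the Aim 1 analysis sections do not carry, and prehospital anaesthesia can fix that score

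*Protocol article*

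**What the plan says.** The Power analysis section of the protocol article states that "a sample size of 242 subjects with severe TBI will provide 90% power" to "detect correlation of 0.22 or higher". The test is two-sided at 0.05, and its null hypothesis is "no correlation between NIRS cerebral oximetry values and admission Glasgow Coma Score". The 242 allows for 29 failed recordings, and 1210 recruits are said to be needed to yield 242 with severe TBI.

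The Aim 1 analysis sections describe something else. The section on new methods opens with "A variety of approaches to signals analysis as commonly utilised in biomedical engineering fields will be undertaken" and uses patients without brain injury as the reference. The next two sections set the resulting methods against cerebral imaging categories and 24-hour and 30-day mortality, and then against three EGOS groups at 6 and 12 months. None of them mentions GCS.

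Outside the Power analysis, GCS has two roles. The first GCS (12 or below, with AIS head 3 or above) defines the severe-TBI subgroup, and the first recorded GCS is an adjustment covariate in the Aim 2 model. Admission GCS is not defined and is not in the list under Early phase outcome data.

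Study design and setting says that the team can anaesthetise, intubate and ventilate at the scene or in transport. Patient event and intervention marking lists "anaesthesia with thiopentone, anaesthesia with ketamine, intubation, institution of mechanical ventilation" among the events marked in real time.

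**The concern.** There are two separate problems.

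**The powered test is not in the analysis.** A power figure belongs to one test on one pair of variables. If the analysis sections never use that pair, a reader will attach the 90% to what they do describe: an open search over signals, tested against imaging, mortality and EGOS. The calculation says nothing about those comparisons.

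**The named score is open to treatment.** Admission follows the prehospital phase. In a patient anaesthetised before arrival, a GCS taken on admission does not measure the injury. If such scores enter the test, the correlation can be diluted. If sedation also moves StO2, a correlation could be produced that has nothing to do with injury. The rest of the article uses the first GCS, which is less exposed, so the Power analysis and the other sections should be reconciled.

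**Working it through.** **1. Reproducing the stated size.** Inputs from the Power analysis: r = 0.22, two-sided 0.05, power 90%. With Fisher's z for one value pair per patient:

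n = ((1.960 + 1.282) / atanh 0.22)² + 3 = (3.2415 / 0.22366)² + 3 = 213.06

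- 213 + 29 = 242, and 29/242 = 12.0%.
- 242/1210 = 20.0%.
- Power at n = 213 is Φ(0.22366 × √210 − 1.960) = 90.0%.

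The figure is sound for the test it names.

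**2. Where that test appears.**

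| Section | What is tested or used | GCS |
|---|---|---|
| Power analysis | NIRS value against GCS | admission |
| New methods for Aim 1 | signal patterns, controls as reference | none |
| Acute phase outcomes (Aim 1) | imaging categories, mortality | none |
| Long-term outcomes (Aim 1) | EGOS groups | none |
| Subgroups | definition of severe TBI | first |
| Statistical analysis for Aim 2 | adjustment covariate | first recorded |

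The pair of variables behind the 90% occurs only in the first row.

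**3. What anaesthesia could do to the power.** The documents give no share anaesthetised and no rule for scoring GCS in such patients, so everything here is an assumption. Model: 213 patients, latent correlation 0.22, GCS cut into the ten scores 3 to 12 with equal frequency, and anaesthetised patients scored 3. With nobody anaesthetised, power is about 88%, slightly below 90% because the score is discrete. Two allocations bound the effect:

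| Share anaesthetised | Lowest-GCS patients anaesthetised: mean r, power | Anaesthesia unrelated to GCS: mean r, power |
|---|---|---|
| 25% | 0.21, about 86% | 0.14, about 55% |
| 50% | 0.19, about 80% | 0.10, about 31% |
| 70% | 0.17, about 71% | 0.07, about 18% |

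Repeat runs differ by a point or two. A mixed case lies between the bounds: if 90% of those with GCS 8 or below and 10% of the rest are anaesthetised (58% overall), r is about 0.17 and power about 70%. Which patients are anaesthetised matters at least as much as how many.

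**4. Whether 90% would carry over to first GCS.** The severe-TBI set is selected on first GCS of 12 or below, so a test of first GCS within it is restricted on the tested variable. If 0.22 already describes such a set, 90% stands. If it came from a wider range, r shrinks. Keeping the lowest 90, 70 or 50% of a normal scale (illustrative cuts) gives r of about 0.188, 0.155 or 0.134. With power = Φ(atanh r × √210 − 1.960):

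- r = 0.188: 79%
- r = 0.155: 62%
- r = 0.134: 50%

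**The case against.** The Power analysis does name the test: its variables, level, sidedness and a time-series regression. The Aim 1 section includes time-series analysis and calls its list of methods non-exhaustive. This is a condensed article whose analysis plan is not shown, so the test may be set out there. A reader might therefore infer too much from the gap, namely that the test will never be run. The documents do not show that. They do show that the one test behind the Aim 1 size is missing from the sections that say what Aim 1 methods are tested against. An open-ended list of exploratory methods does not supply a specific hypothesis test. Absence from the early outcome list proves little, since first recorded GCS is not listed there either although the Aim 2 model uses it.

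A reader might also infer that treatment determines admission GCS in many patients. Nothing supports that. The article shows only that anaesthesia can be given and is marked. The steep losses (55, 31 and 18%) need anaesthesia to be unrelated to GCS. If it goes to the patients with the lowest scores, most of the power remains. Because sedation might also create correlation, even the direction of the error is open.

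A third inference is that the whole cohort size is unsupported. That goes too far. The same section gives Aims 2 and 3 their own statements, a 95% interval of 49% to 63% around 56% and 80% power for a trend test across EGOS groups, and neither rests on GCS. At n = 213 the half-width is 1.96 × √(0.56 × 0.44 / 213) = 6.7 points, in line with that interval.

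**Conclusion.** The point holds in a limited form. The mismatch needs no assumption: the 90% is for NIRS values against admission GCS, and it covers none of the imaging, mortality or EGOS comparisons in the Aim 1 sections. The choice of admission GCS is a second weakness, because treatment before arrival can fix that score and the article elsewhere relies on the first GCS.

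The size of this second effect is unknown. Under the assumed shares of 25 to 70%, power runs from about 86% down to 71% under one allocation and from about 55% down to 18% under the other. Neither is a forecast for this cohort. Range restriction is a condition on any revised power statement and not a proven fault, because the article does not give the GCS range behind r = 0.22.

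**What to change.** - In the Power analysis, replace admission GCS with the first recorded GCS, and use the real-time event marks to confirm that it precedes anaesthesia.
- Add one prespecified test to the Aim 1 analysis: a single StO2 summary per patient against that score in the severe-TBI set. This matches the one-pair-per-patient arithmetic behind 213.
- State that the power figure covers this test only, and not the exploratory signals analyses or the imaging, mortality and EGOS comparisons.
- Do not carry the 90% over unqualified. Say that it assumes r = 0.22 within the set with first GCS of 12 or below, and that power is lower if 0.22 came from a wider range (for example about 79% at r = 0.188 and 62% at r = 0.155, with n = 213).

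Cost: protocol wording, one extra analysis, and a narrower and possibly lower power statement. First recorded GCS and the event marks are already part of the study, so no new data or patients are needed.

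### The sample size allows only for failed NIRS recordings, yet the same number is carried to a six-month telephone outcome with no stated allowance for non-consent or loss to follow-up

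*Protocol article*

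**What the plan says.** The Power analysis section of the protocol article states that "a sample size of 242 subjects with severe TBI will provide 90% power to detect correlation of 0.22 or higher", "in a 2-sided 0.05 level test of the null hypothesis of no correlation". The correlation is between NIRS cerebral oximetry and admission GCS. One loss is allowed for: "adjusting for 29 (approximately 12%) unsuccessful NIRS monitoring data collection attempts". On total recruitment, a historical mission database is said to show that "1210 total recruits will be required to incorporate 242 subjects with severe TBI".

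For the other aims the section says: "To address Aims 2 and 3, the same number of subjects will be enough". Two claims follow for six-month EGOS: an incidence of 56% with a 95% interval of 49% to 63%, and 80% power for a trend test across EGOS groups expected at 30% deceased, 20% poor outcome and 50% good outcome.

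Three other sections bear on how many patients reach that endpoint:

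- Inclusion and exclusion criteria lists as an exclusion: "Patients where follow-up consent is not later obtained from the patient or family".
- Research ethics describes an initial consent waiver, with consent sought during follow-up, that is, after monitoring has ended.
- Long-term outcomes, on assessment at 6 and 12 months: "Follow-up by the research nurse will be undertaken via phone interview with the patient or appropriately identified relative".

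**The concern.** The article describes two ways of losing a patient after a successful recording: consent is not obtained, or the patient or relative is not reached by telephone. Neither appears in the sample-size calculation. The allowance that is stated concerns recording failure alone, and it appears to be fully spent in reaching the number needed for Aim 1. Carrying the same number to six-month EGOS then assumes, without saying so, that every successfully monitored patient consents and has a known outcome.

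What is at stake is mainly the 80% trend power, and with it Aim 3, which rests wholly on follow-up outcomes. This is more than a detail left to a fuller document, because the article itself gives the adjustment, names a single loss, and attaches figures for power and precision to the six-month endpoint.

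**Working it through.** **Inputs from the article.** r = 0.22, power 90%, two-sided alpha 0.05, 242 severe-TBI patients, 29 failed recordings, 1210 recruits, incidence 56% (49% to 63%), trend power 80%, 30% expected deaths (all in Power analysis).

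**Assumed input.** The article gives no rate for non-consent or loss to follow-up. A further loss of 10, 20 or 30% is used below as a range.

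**1. The plan's Aim 1 figure reproduces.** By Fisher z, n = ((1.960 + 1.2816)/atanh(0.22))² + 3 = 213.06. Power at 213 is 89.99%. Then 213 + 29 = 242, and 29/242 = 12.0%. The 29 failed recordings therefore account for the whole difference between 242 and the number required.

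**2. No second margin is visible in 1210.** 242/1210 = 0.200 exactly, a flat share of severe TBI.

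**3. What the printed interval shows.** Wald interval: 0.56 ± 1.96 × √(0.56 × 0.44/n).

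- n = 242: 49.7% to 62.3%, which rounds to 50% to 62% and does not match.
- n = 213: 49.3% to 62.7%, which rounds to 49% to 63% and matches.
- Every n from 169 to 224 rounds to 49% to 63%. From 213, that covers a further loss of up to 1 − 169/213 = 20.7%.

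The interval shows that 242 was not used. It is consistent with 213 but does not establish it.

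**4. Trend power under further loss.** The trend calculation cannot be reproduced, because neither the NIRS-group shares nor the effect in test units is given. It can be scaled from the stated 80%, taken to hold at 213: power = Φ((1.960 + 0.8416) × √(n/213) − 1.960).

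| Assumed further loss | n, loss in all patients | Trend power | 95% interval for 56% | n, loss in survivors only | Trend power |
|---|---|---|---|---|---|
| 10% | 192 | 76% | 49.0 to 63.0% | 198 | 77% |
| 20% | 170 | 71% | 48.5 to 63.5% | 183 | 74% |
| 30% | 149 | 65% | 48.0 to 64.0% | 168 | 70% |

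The survivors-only n is 213 × (0.30 + 0.70 × (1 − loss)). If the stated 80% was computed at 242 instead, loss in all patients gives about 70, 65 and 59%.

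**5. Aim 1, only if non-consenters are counted within the 242.** Power = Φ(atanh(0.22) × √(n − 3) − 1.960). With 10% non-consent (n = 192) it is 87%; with 20% (n = 170) it is 82%.

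**The case against.** The strongest reply is that the stated figures reproduce, so nothing has been miscalculated, and that a condensed article on an observational cohort need not set out every attrition assumption. The first half stands: the gap is an unstated assumption, not an arithmetic slip. The second half carries less weight, because the article does state its adjustment and then makes quantitative six-month claims on that basis.

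Four further limits stand:

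- **The interval proves little.** A reader might infer from 49% to 63% that exactly 213 patients with no loss were assumed. The documents do not support that, since any n from 169 to 224 gives the same rounded figures. Precision is barely affected up to about 20% loss.
- **Six-month loss does not reach Aim 1.** A reader might apply one combined loss to every aim and conclude that the 90% falls too. The Aim 1 correlation is with admission GCS, which is known whether or not the patient is later reached by telephone. Only non-consent could reduce it.
- **The consent basis is open.** Lack of consent is an exclusion criterion, and the article allows exclusions to be applied later. The 242 may therefore already be net of non-consenters. Nothing says so, and the article does not describe how the database yielded 1210, but the opposite reading cannot be asserted as fact.
- **Deaths need no telephone call.** About 30% are expected to die, and hospital records supply 30-day mortality and survival to discharge. A relative may also answer for a survivor. Telephone loss thus falls mainly on survivors, whereas non-consent can affect anyone.

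It is also tempting to express the loss as a detectable odds ratio. That would need the shares of patients in the NIRS groups, which the article does not give; the split between groups 2 and 3 is at a median still to be determined.

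**Conclusion.** The point holds in a limited form. The only stated allowance is 29 failed recordings, which takes 242 to the 213 needed for Aim 1 and leaves nothing for non-consent or loss to follow-up. The same number is nevertheless said to suffice for an endpoint collected by telephone at six months.

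The main consequence is for the 80% trend power, which falls to about 76, 71 or 65% for 10, 20 or 30% loss among all patients, or to between about 77 and 70% if 10 to 30% of survivors alone are lost. These figures rest on assumed loss rates, on the stated 80% applying at 213, and on scaling, since the test itself cannot be reproduced. The effect on the interval is small. The effect on Aim 1, 87% or 82% at 10% or 20% non-consent, is conditional on the 242 including patients who later do not consent.

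**What to change.** Keep recruitment at 1210 and amend the Power analysis section in three places:

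1. State whether 242 and 1210 count patients before or after the consent exclusion.
2. State an assumed rate of loss at six months, separating non-consent from failed telephone contact, and restate the EGOS trend power and interval on the number evaluable at that time.
3. Restate Aim 1 power for non-consent only, and only if non-consenters are within the 242.

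The cost is a few sentences and no extra patients. Preserving 213 evaluable patients at six months would cost more: with 10% loss, 242/0.90 gives 269 severe-TBI patients and 269 × 5 = 1345 recruits; with 20%, 242/0.80 gives 303 and 1515. Restating the figures at fixed recruitment is the proportionate change.
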